## Abstract

**Background:**

Glenohumeral osteoarthritis can, in the most severe cases, require surgery with insertion of a shoulder arthroplasty. A design with a stem in the humeral bone canal is currently regarded as the standard treatment option in patients who have an intact rotator cuff function, but complications related to the stem including humeral fractures can have devastating consequences. By using a stemless humeral component, stem-related complications can be reduced. The aim of this study is to compare the Comprehensive Nano stemless total shoulder arthroplasty (intervention group) with the Comprehensive stemmed total shoulder arthroplasty (control group).

**Materials and methods:**

This is a randomized controlled trial comparing the stemless and the stemmed total shoulder arthroplasty. All Danish citizens with glenohumeral osteoarthritis indicating a total shoulder arthroplasty referred to the orthopedic department at Copenhagen University Hospital in Herlev/Gentofte will be offered participation. The following exclude from participation: below 18 years of age, cognitive or linguistic impairment, insufficient function of the rotator cuff, poor bone quality, and ASA groups 4–5. A total of 122 patients will be included of which 56 will be part of a radiostereometric analysis (RSA) study of humeral component migration. The primary outcomes are magnitude of migration of the humeral component assessed by RSA and patient-reported outcome by Western Ontario Osteoarthritis of the Shoulder index (WOOS). The secondary outcomes are additional patient-reported outcomes, functional outcome, readmission, complications, revisions, and changes in bone mineral density (BMD) of the proximal humerus assessed by duel energy x-ray absorptiometry (DXA) and economy (cost-utility analysis). The patients are examined before the operation and 3, 6, 12, and 24 months postoperative.

**Discussion:**

To our knowledge, RSA has never been used to access migration of a stemmed or a stemless humeral component nor has the stemmed and the stemless humeral component been compared with regard to pain relief and shoulder function in a randomized clinical trial. Today, the two designs are considered equal in the treatment of osteoarthritis. The study will provide surgeons and patients with information about shoulder arthroplasty for osteoarthritis and assist them in decision-making.

**Trial registration:**

ClinicalTrials.gov NCT04105478. Registered on 25 September 2019

## Background

Previous literature has shown that anatomical total shoulder arthroplasty (an artificial shoulder joint with replacement of both the humeral head and the glenoid cavity) is an effective treatment of end-stage glenohumeral osteoarthritis with pain relief and significant improvement in shoulder function [1–4]. The outcome is better than the outcome of hemiarthroplasty (an artificial shoulder joint with replacement of only the humeral head), and it is recommended by the American Academy of Orthopedic Surgeons in patients with painful osteoarthritis and an intact rotator cuff function [5]. A stemmed humeral component applied either with or without cement is commonly used and is currently considered to be the gold standard. Nevertheless, complications related to the stemmed humeral component can have devastating consequences [6].

The prevalence of periprosthetic humeral fractures after total shoulder arthroplasty is between 1.6 and 2.4% [6]. These patients can be treated either non-surgically with risk of non-union or mal-union or they can be treated surgically, which, in most cases, is technically demanding. Removal of a well-fixed humeral stem is difficult and may result in additional fracture or destruction of the humeral bone and the outcome is often disappointing [7–10].

The stemless humeral component is fixed only in the metaphysis (the wide portion of the long bones where bone growth occurs in childhood). By using this stemless metaphyseal fixation, the risk of a periprosthetic fracture and other stem-related complications can be reduced. There are also other advantages of the stemless design [11]. When using a stemmed humeral component, the inclination (the angle between the head and the shaft of the humerus) is given in advance. Even though the modern designs have variable inclination options to choose from, it can be difficult to restore the anatomy. With preoperative planning and precise cutting instrumentation of the stemless humeral component, the individual anatomy can, in theory, be more easily restored. In addition, the stemless design may be associated with shorter operation time compared with the stemmed design. Finally, because of the canal preserving design, the revision procedure is facilitated should the need of a revision arthroplasty arise, making the stemless design easier revisable. However, this is probably not as important as it used to be, since most modern stemmed designs have a common platform system which allows the stem to be retained in the case of revision to a reverse shoulder arthroplasty due to rotator cuff problems. The theoretical advantages of the stemless design may lead to a superior functional outcome compared with the stemmed total shoulder arthroplasty.

However, the stemless humeral component relies extensively on good metaphyseal bone quality, and the risk of osteolysis, stress shielding, and aseptic loosening may be higher than for the stemmed humeral component with peripheral fixation where the bone quality and density is superior to the central bone [12, 13]. This may lead to a higher risk of migration of the component.

Plain radiographs are unable to detect minor implant migration, and authors have recommended that radiostereometric analysis (RSA) should be used instead [14, 15]. By inserting small tantalum beads (0.8 mm) on the arthroplasty component and into the surrounding bone, implant migration can be measured extremely accurately [16]. Technical advances within RSA have made it possible to identify the implant and its position using the geometry of the implant instead of attaching tantalum beads to the implant (model-based radiostereometric analysis, MB-RSA). The MB-RSA technique is less precise than the marker-based method. However, precision error values are still acceptable for clinical studies aimed at evaluating implant migration [17]. The use of RSA for evaluation of implant migration has been used frequently in the evaluation of hip and knee arthroplasty surgery. It has been shown that the trend for late implant aseptic loosening of the tibial component in total knee arthroplasty is consistent with early RSA findings of continuous migration past the first postoperative year [18]. Therefore, it has been suggested that a small series of a new arthroplasty should be monitored with RSA the first 2 years postoperatively, as a part of a safe phased introduction of new arthroplasties [19–21].

Changes in bone mineral density (BMD) in close relation to an orthopedic implant can be measured by dual-energy x-ray absorptiometry (DXA) [22, 23]. The use of DXA for prospective quantitative evaluation of implant induced adaptive bone remodeling has been widely used after both hip and knee primary replacement surgery [24–28]. Only few studies [29, 30] have evaluated changes in BMD after shoulder arthroplasty. After an initial decrease, probably caused by postoperative immobilization [31], BMD of the proximal humerus increased and was higher than the initial value at follow-up 1 and 2 years postoperatively [30].

In shoulder surgery, RSA has been used to study the migration of the glenoid component [32, 33] and, in few cases, migration of hydroxy-coated resurfacing humeral components [30, 34]. To our knowledge, RSA has never been used to access migration of a stemmed or a stemless humeral component nor has the stemmed and the stemless humeral component been compared in a randomized design with regard to clinical outcome and patient-reported outcome.

The aim of this study is to compare the Comprehensive Nano stemless total shoulder arthroplasty (intervention group) with the Comprehensive stemmed total shoulder arthroplasty (control group). Our hypotheses are:
The Comprehensive Nano stemless total shoulder arthroplasty will migrate more than the Comprehensive stemmed total shoulder arthroplasty.The Comprehensive Nano stemless total shoulder arthroplasty will have a superior functional outcome compared with the Comprehensive stemmed total shoulder arthroplasty.

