### Randomization

Based on the sample calculation, we intend to include a total number of 122 patients of which the first 56 patients who agree to participate will be studied using MB-RSA and DXA. The patients are allocated into two groups of equal of size and equally randomized to both arms:
The uncemented Comprehensive Nano stemless shoulder arthroplasty (intervention group)The uncemented Comprehensive stemmed total shoulder arthroplasty (control group)

The randomization is done in the operating theater using the trial laptop just after the perioperative evaluation of the bone-stock and the rotator cuff. Therefore, the patient is anesthetized when the randomization is done. The randomization is done using a computerized irreversible application—the Research Electronic Data Capture (REdCap). The randomization sequence will be computer generated by block randomization stratified for age and gender. The patients are equally randomized to both arms (1:1 allocation). The randomization table has been prepared by an independent statistician.

The patients and the outcome assessor will not be blinded to the randomization allocation. However, the statistician associated with the trial will be blinded.

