#### Secondary radiological outcomes

##### DXA

Fifty-six patients will be included in this part of the study. DXA will be performed preoperatively to evaluate BMD of the proximal humerus and distal forearm. Bilateral BMD measurements of the proximal humerus and distal forearm will be used to adjust for changes in BMD that are not related to the shoulder arthroplasty. The primary value of interest is the difference in mean BMD between the preoperative score and 2-year follow-up. The precision of DXA will be evaluated by double examinations.

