### Statistics

The nature of data is evaluated before the analysis. The between-group differences are expected to be analyzed with independent *t* test (Student *t* test). If the assumption of normal distribution is violated, then data will be analyzed with non-parametric tests. We do not expect the RSA data to be normal distributed. These data will be analyzed with non-parametric analysis using the Friedmann test for migration over time and the Mann-Whitney *U* test for between-group differences. We expect the DXA data to be normally distributed and changes over time will be evaluated by a parametric analysis using a paired *t* test. Potential between-group differences in BMD changes will be analyzed with independent *t* test (Student *t* test). In addition, due to the nature of repeated measures in this study, we intend to analyze the overall results according to a mixed effects model [45]. The difference between pre- and postoperative scores is expected to be analyzed as a secondary endpoint with parametric analysis using a paired *t* test. Since the two primary endpoints are distinct, multiple testing adjustments will not be performed.

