The patients will not be blinded to their randomization allocation. This would be very difficult in Denmark, as patients have access to their records electronically. However, this is not expected to be of great significance as the patients hardly have an expectation of one of the prostheses to be the superior. Furthermore, it is not possible to blind the outcome assessor as it is the same person analyzing the RSA and DXA, in which one must necessarily have access to the radiographs. However, this is not expected to be of any significance to the second primary outcome, since this is a patient-reported outcome which is completed by the patient independently of the outcome assessor. In addition, the final analyses will be carried out by a blinded statistician associated with the trial.

In a study based on data from the Nordic Arthroplasty Register Association [47], the total stemless shoulder arthroplasty and the total stemmed shoulder arthroplasty appear to have comparable short-time survival. However, it is not known whether they continue to perform equally. Ryd et al. [18] and Kärrholm et al. [48] both found a relationship between short-term RSA results and future loosening of prostheses. They found that already 1-year postoperative RSA can be used to identify prostheses at risk of future loosening. Therefore, the use of RSA in this study will enable us to predict the long-term results of the two arthroplasties.

The main value of the study is new knowledge about the best treatment option for end-stage osteoarthritis. This can be of value to future patients with end-stage osteoarthritis where shoulder arthroplasty is considered.

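### The between-arm test of 2-year migration is unadjusted: it leaves out age, gender and preoperative humeral BMD, and may give up precision the trial could have at almost no cost

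*Protocol article*

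**What the plan says.** The Background section gives the reason for expecting more migration with the stemless implant: "the stemless humeral component relies extensively on good metaphyseal bone quality", whereas the stemmed component is fixed in denser peripheral bone. It adds: "This may lead to a higher risk of migration of the component". The first hypothesis is a plain comparison of arms: "The Comprehensive Nano stemless total shoulder arthroplasty will migrate more than the Comprehensive stemmed total shoulder arthroplasty".

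Under Randomization, allocation is stratified for age and gender and takes place "just after the perioperative evaluation of the bone-stock and the rotator cuff". The first 56 consenting patients have both RSA and DXA. Under DXA, "DXA will be performed preoperatively to evaluate BMD of the proximal humerus and distal forearm"; the stated value of interest is the change in BMD from before surgery to 2 years. Under Statistics, the RSA data are expected not to be normal and are to be analysed with the Friedman test over time and "the Mann-Whitney *U* test for between-group differences". A mixed effects model is also intended for the overall results, with no covariates listed.

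On eligibility, the abstract lists among its exclusions "insufficient function of the rotator cuff, poor bone quality". The exclusion criteria under Method are narrower on bone: insufficient glenoid bone-stock, or humeral cysts over 1 cm on CT, verified perioperatively. The Discussion states the study's value broadly: "The main value of the study is new knowledge about the best treatment option for end-stage osteoarthritis".

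**The concern.** The protocol names one biological factor, the quality of the humeral bone, as relevant to stemless fixation. It measures a direct proxy for that factor before surgery in every RSA patient, and it stratifies on two further variables. The between-arm test named for the primary radiological outcome uses none of them. No stated analysis relates baseline BMD to migration.

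With 22 to 28 patients per arm, unexplained variation is the main limit on this comparison. If baseline BMD predicts migration, the stated test leaves that variation in the noise. At stake are a wider interval around the arm difference and a harder reading of a borderline or null RSA result. A smaller matter is scope: the Discussion limits transfer of the results by surgeons' skill and does not mention the selection on bone that precedes randomisation.

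**Working it through.** **1. The plan's own figure.** Inputs from Sample size calculation RSA: SD 0.4 mm, difference 0.4 mm, 5% significance (two-sided assumed), power 0.90, 20% drop-out.

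n per group = 2 × (z₀.₉₇₅ + z₀.₉₀)² × (SD/difference)² = 2 × (1.960 + 1.282)² × 1 = 21.01, rounded up to 22. With drop-out, 22/0.8 = 27.5, rounded up to 28, so 56 in total. This agrees with the protocol. Exact t-test power at 22 per group is 0.900. The size is therefore adequate for an unadjusted comparison of means.

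**2. What adjustment could add.** Let r be the correlation of preoperative BMD with suitably transformed MTPM. The documents do not give r; 0.3 to 0.5 is assumed. Residual variance is multiplied by 1 − r², and the equivalent sample size by 1/(1 − r²). The unadjusted standard error at 22 per group is 0.4 × √(2/22) = 0.121 mm, and adjustment multiplies it by √(1 − r²).

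| r (assumed) | 1 − r² | 1/(1 − r²) | Standard error, mm |
|---|---|---|---|
| 0.3 | 0.91 | 1.10 | 0.115 |
| 0.4 | 0.84 | 1.19 | 0.111 |
| 0.5 | 0.75 | 1.33 | 0.104 |

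These figures hold for a linear model. They ignore the small cost of estimating the coefficients: one degree of freedom each for BMD, age and gender, so 42 − 3 = 39 residual degrees of freedom with 44 patients. At r = 0.3 that cost takes back part of the gain. If r is near zero there is no gain.

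**3. Chance imbalance.** The standardised BMD difference between arms has standard error √(2/22) = 0.30 or √(2/28) = 0.27, so 95% of randomisations fall within about ±0.59 or ±0.52 SD. The shift in the MTPM difference at those limits is r × imbalance × 0.4 mm: from 0.3 × 0.52 × 0.4 = 0.06 mm to 0.5 × 0.59 × 0.4 = 0.12 mm, or about 16 to 30% of the 0.4 mm target. This is random error that the test already allows for, not bias. Adjustment removes the part that BMD explains.

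**4. What an arm-by-BMD term could show.** Take a median split with equal cells (assumed) and SD 0.4 mm. The standard error of the difference of differences is 0.4 × √(16/N): 0.241 mm for N = 44 and 0.214 mm for N = 56. Power for a 0.4 mm interaction is Φ(0.4/0.241 − 1.96) = 38% and Φ(0.4/0.214 − 1.96) = 46%. For 0.2 mm it is 13% and 15%. Such a term can only be exploratory.

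**5. The bone criteria side by side.** The abstract excludes poor bone quality without qualification. The criteria under Method concern glenoid bone-stock and large humeral cysts, with no BMD or osteopenia cut-off; under Enrolment, DXA is used to evaluate osteopenia. On the criteria under Method, patients with low humeral BMD can be randomised, so a range of BMD should remain to adjust for. The two descriptions do not match.

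**The case against.** The strongest reply is that nothing in the primary test is wrong. Hypothesis 1 is a difference between arms and can be tested without its mechanism. The Background argument concerns central against peripheral fixation, a contrast that exists within any patient and does not require weak bone. Checking eligibility before randomisation affects both arms alike and protects internal validity. All of this stands.

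It can also be said that covariates are commonly left to an analysis plan that is not shown, and that the mixed model may include some. This stands only in part. The protocol does not leave the RSA comparison open: it names the test, and in its ordinary form that test takes no covariate. A better-specified companion to a stated method is a fair suggestion. That the gain rests on an assumed correlation is true, and the working shows the range.

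A reader might infer more: that patients with poor humeral bone are removed before randomisation, so that the trial cannot show whether stemless migration depends on bone quality. The documents do not support this. The criteria under Method set no BMD limit, and BMD and MTPM are both collected in the same 56 patients, so the relation can be examined, though weakly. Nor is effect modification by bone quality a stated aim. The Discussion sentence on end-stage osteoarthritis describes the study's value and is not a trial conclusion, so only a modest qualification of scope is warranted.

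**Conclusion.** The point holds as a limited improvement, not as an error. The stated Mann-Whitney comparison is valid but leaves out the two stratification factors and a baseline measure that the protocol itself presents as relevant to stemless fixation. The possible gain from BMD is about 10 to 33% in equivalent sample size, under an assumed correlation of 0.3 to 0.5 and a roughly linear relation after transformation; it would be smaller if the correlation is weaker. An interaction with BMD cannot be settled at this size. Two wording matters go with it: the scope of the RSA result, and the mismatch between the abstract and the exclusion criteria under Method. Severity is low.

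**What to change.** - **Statistics:** keep the Mann-Whitney test. Prespecify beside it a between-arm comparison of 2-year MTPM, by ANCOVA on log-transformed or ranked values, adjusted for age, gender and preoperative proximal humeral BMD of the operated side. Report the estimate with its confidence interval. Fix this before the RSA data are analysed.
- **Interaction:** if an arm-by-BMD estimate is given, label it exploratory and show its confidence interval.
- **Discussion:** state that the RSA result applies to patients who meet the bone-related eligibility criteria and pass the intraoperative bone-stock evaluation.
- **Abstract and Method:** reconcile the two descriptions of the bone exclusion.

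All the data are already being collected. The cost is a few sentences, one extra model and a slightly narrower stated conclusion.

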## Methods and design

### Study design

This is an investigator-initiated, single-center, 1:1 randomized controlled, superiority trial with parallel groups, comparing the Comprehensive Nano stemless total shoulder arthroplasty (intervention group) with the Comprehensive stemmed total shoulder arthroplasty (control group). Both implants are manufactured by Zimmer Biomet (Warsaw, IN, USA).

### Method

Inclusion criteria:
Primary glenohumeral osteoarthritis independent of previous joint preserving surgeryOsteoarthritis on plain radiographs with standard anterior-posterior and lateral projectionsInsufficient effect of non-surgical treatment with symptoms severe enough to justify shoulder arthroplasty.ASA scores 1–3, physically fit for surgery and rehabilitation

Exclusion criteria:
Below 18 years of ageCognitive or linguistic impairmentRotator cuff insufficiency defined as rotator cuff lesions or grade 2 fat infiltrations on MRI according to the Goutallier classification [35, 36] verified with impaired functional strength and perioperative findingsInsufficient glenoid bone-stock or large (> 1 cm) humeral bone cysts on CT verified with perioperative findingsASA scores 4–5

### Enrolment

All Danish citizens with glenohumeral osteoarthritis indicating an anatomical total shoulder arthroplasty referred to the orthopedic department at Copenhagen University Hospital in Herlev/Gentofte will be considered for participation in the trial. The treating physician will review the medical records and assess whether the patient fulfills the above-mentioned inclusion criteria and none of the following exclusion criteria. If so, the treating physician will pass on the information to the responsible investigator (Fig. 1) and the patient will be offered participation.

**Fig. 1 Fig1:**
[figure not shown]
CONSORT flow diagram. The expected flow of patients through the study

The patients will be called in for an undisturbed consultation with the treating physician. If the treating physician considers the patient suitable for inclusion in the project, the patient will receive oral and written information regarding the study. Furthermore, they will be informed about the possibility to bring a bystander for the preparation consultation with the corresponding investigator. The preparation consultation with the corresponding investigator will then be held at least 24 h later in an undisturbed ambulatory room. At this consultation, the patient (and a possible bystander) will once again receive information regarding the study and subsequently the informed consent will be obtained. The patient has thus been given at least 24 h of reflection time, as well as being given the opportunity to bring a bystander.

The informed consent will give the primary investigator access to information about comorbidity, medication, education, occupation, age, and gender. The patients will then be asked to complete 4 questionnaires (Oxford Shoulder Score, Western Ontario Osteoarthritis of the Shoulder index, EQ-5D-5L, and pain). They will also have a clinical examination with measurement of pain, activity of daily living, range of movement, and strength (Constant-Murley score) and a radiographic examination with plain radiographs with standard anterior-posterior and lateral projections, CT scan, and MRI of the index shoulder joint. Finally, DXA is used to evaluate osteopenia and BMD of the proximal humerus and distal forearm. There are no plans of additional studies or use of data beyond this trial.

